### **7.3.6. Histopathology**

The resected polyps will be submitted for histologic examination by one expert pathologist at each site. Before the trial starts, a consensus meeting will be held for all participating pathologists to standardize the examination procedure and to gain consensus on the classification criteria. If any uncertainty or doubt exists, an expert in gastrointestinal pathology will serve as the adjudicator to perform a second review and make the final decision. All of the pathologists (including the final adjudicator) who will perform the histopathologic examinations and produce the pathology assessment will be blinded to the assigned study arm of the specimens. The pathology reports of the subjects will be kept securely at each site as the source data.

### **7.3.7. Withdrawal of Subjects**

Participation in the study is completely voluntary, thus subjects can withdraw at any time during or after the procedure. Written consent will be obtained from all subjects. Withdrawing from the procedure has no negative implication on their colonoscopy examination and subsequent clinical care. A subject may be withdrawn from the research at the discretion of the endoscopist or the investigator. Subjects who meet any of the following withdrawal criteria may be withdrawn from the study.

Withdrawal criteria:

- (1) Subject who withdraws consent.
- (2) Poor bowel preparation based on the four-grade modified Aronchick Bowel Preparation Scale.
- (3) There is a clinical suspicion for hereditary polyposis syndrome or new case of IBD based on the colonoscopy per the investigator's judgement.
- (4) The colonoscopy procedure cannot be completed, either due to intolerance, stenosis, obstruction, huge occupying lesions, or solid stool.
- (5) The colonoscopy procedure is terminated due to any procedure-related complications.
- (6) Subjects with difficult anatomy or post-surgical anatomy preventing completion of the procedure using a standard colonoscope.

## **7.4. Endpoints**

### **7.4.1. Primary Endpoint**

The primary endpoint is the ADR of the CC as compared with that of the SC. The ADR is defined as the percentage of subjects undergoing a complete colonoscopy, who have at least one histologically confirmed adenoma detected and removed.

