### **7.2. Study Population**

#### ***7.2.1. Inclusion criteria***

- (1) Age of  $\geq 40$  years and  $< 80$  years
- (2) Subjects who have given a signed informed consent form
- (3) Informed consensus has been obtained that endoscopic resection should be performed if a lesion is found
- (4) Subjects who are scheduled for screening or diagnostic colonoscopy for colorectal cancer (CRC) or surveillance colonoscopy for post-polypectomy follow-up

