### **7.3.4. Blinding**

The subject and the pathologist who performs the histopathological review will be blinded to the received procedure, while the operator will not be blinded to the study arm assigned to the subject. The investigator at each site will be unblinded to the assigned study arm of the subject, but will be blinded to the assigned study arm of the specimens when conducting the histopathological review

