### **7.3.5. Colonoscopy Procedures (Intervention Visit)**

- (1) The subjects will undergo standard bowel preparation and routine pre-procedure examination for colonoscopy (standard of care)
- (2) The colonoscopy (CC or SC) will be performed by qualified endoscopists, who are board-certified gastroenterologists or board-certified colorectal surgeons, using the endoscopy video processor specified in Section 7.5.
- (3) During the colonoscopy, real-time video will be recorded.
- (4) All proximal polyps, and polyps  $\geq 0.6$  cm found at sigmoid, rectosigmoid junction, and rectum will be resected for histopathological examination.

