## 8. Statistical Analysis

## 8.1. Sample Size Estimation

The sample size is calculated based on the evaluation of primary outcome ADR. Based on the results of meta-analysis, an expected ADR ranges from around 20% to 40% for AI-aided colonoscopy and SC ([Barua et al., 2021](#); [Hassan et al., 2021](#); [Mohan et al., 2020](#); [Shaukat et al., 2021](#); [Spadaccini et al., 2021](#)). A sample size ranging from 198 to 297 per arm is required to establish non-inferiority with a non-inferiority margin of 10%, power of 80% and an alpha level of 2.5% (one-sided). Considering a withdrawal rate of 10% due to potential exclusions and drop-outs, the enrollment goal is 220 to 330 subjects per arm.

However, interim analysis of this study in March 2023 showed that the ADR in our SC group is 49%, which is significantly higher than the ADR results acquired from meta-analysis (around 20%); therefore, the enrollment goal is increased to 750 subjects per arm. (i.e., 1500 subjects in total. )

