## 8.3. Statistical Methods

The primary analysis will be the comparison of ADR between CC and SC. Differences in ADR between two arms will be expressed as relative risk (RR) with 95% CIs.

Non-inferiority will be met for the primary endpoint (ADR) if the lower 2-sided 95% confidence interval (CI) excludes a 10% or greater difference in favor of the control group. The 10% non-inferiority margin reflects a typical maximum clinically acceptable difference for comparative studies.

If non-inferiority is demonstrated for the primary endpoint, the endpoint will be assessed for superiority (one-sided p value <0.025) using the Fisher exact test.

Categorical variables will be described by frequency counts and percentages. Quantitative variables will be described by mean and standard deviations. Chi-square and t-tests will be used to compare categorical and continuous variables between the two groups, respectively.

ADR and PDR will be stratified by subject characteristics (including age, gender, and colonoscopy indication) and experience of the operator; APC and PPC will be stratified by lesion characteristics (including size, location, and morphology of each polyp).

A p value <0.05 will be considered statistically significant.

All statistical analyses will be performed using R or Python software.

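### For subjects whose only adenomas are distal and under 0.6 cm, ADR status can turn on a removal decision that the protocol leaves to an unblinded operator

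*Protocol*

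**What the plan says.** - **Endpoint (Protocol 7.4.1).** Among subjects with a complete colonoscopy, ADR counts those "who have at least one histologically confirmed adenoma detected and removed". Removal is part of the definition. No size or site is excluded.
- **Resection rule (7.3.5, item 4).** All proximal polyps are resected. For the distal sites, only polyps of at least 0.6 cm "found at sigmoid, rectosigmoid junction, and rectum will be resected for histopathological examination". Nothing is said about smaller polyps there; removal is neither required nor forbidden.
- **Histology (7.3.6).** "The resected polyps will be submitted for histologic examination by one expert pathologist at each site". A polyp left in place is never classified.
- **Blinding (7.3.4).** Subject and pathologist are blinded, but "the operator will not be blinded to the study arm assigned to the subject".
- **Consent (7.2.1, criterion 3).** Subjects agree that "endoscopic resection should be performed if a lesion is found", again without a size or site limit.
- **Analysis (8.3).** Non-inferiority is met if the confidence limit "excludes a 10% or greater difference in favor of the control group"; a one-sided Fisher exact test for superiority at 0.025 follows.
- **Size (8.1).** After the March 2023 interim analysis, "the enrollment goal is increased to 750 subjects per arm".

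**The concern.** The endpoint and the resection rule do not cover the same lesions. Between them lie the small sigmoid, rectosigmoid and rectal polyps, which count if removed but need not be removed. For a subject with no other adenoma, taking out such a polyp can make the subject ADR-positive, and leaving it makes the subject ADR-negative. The person who decides knows the allocation, and the decision comes after randomisation.

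Two things must be kept apart. A small distal adenoma found because the device pointed to it is a true effect of the device. Bias arises only if polyps that were seen are removed more often in one arm than in the other. Blinded pathology cannot repair that, because the selection takes place before any specimen exists. A spurious shift towards computer-aided colonoscopy (CC) would inflate the error of both the non-inferiority and the superiority test. A shift towards standard colonoscopy (SC) would cost power.

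**Working it through.** **Step 1: the passages side by side.** I read proximal as proximal to the sigmoid, since the rule treats sigmoid, rectosigmoid junction and rectum separately.

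| Polyp | Resection under 7.3.5(4) | Counts in ADR under 7.4.1 if an adenoma |
|---|---|---|
| Proximal, any size | required | yes |
| Sigmoid, rectosigmoid or rectal, 0.6 cm or more | required | yes |
| Sigmoid, rectosigmoid or rectal, under 0.6 cm | not stated | yes, if removed |

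Only the third row is open. It sets a subject's status only when the subject has no adenoma in the first two rows.

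**Step 2: does criterion 3 close the third row?** It is an eligibility condition about the subject's agreement to resection. Read as the operating rule for every lesion, it would leave the 0.6 cm threshold with no purpose. It does not settle the matter.

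**Step 3: how unequal removal would enter the result.** The protocol gives no figure for this, so there is none to reproduce. Let f be the share of subjects whose only adenomas are small, distal and seen, and g the difference between arms in the probability of removing them. Then

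spurious shift in the ADR difference = f × g.

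Neither f nor g is in the protocol. A 1-point shift needs, for example, f = 5% with g = 20 points (0.05 × 0.20 = 0.01), or f = 2% with g = 50 points. With f = 2% and g = 10 points the shift is 0.2 points. If g = 0 there is no bias.

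**Step 4: what a given shift would do (illustration).** Inputs:
- 750 per arm and 10% withdrawal (8.1): 750 × 0.9 = 675 evaluable per arm.
- SC ADR 49% (8.1, March 2023 interim analysis).
- The 10% margin read as 10 points on the ADR difference (assumption).
- One point is 0.01 × 675 = 6.75, about 7 CC subjects.

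Method: exact enumeration of two independent binomials. Superiority is one-sided Fisher p < 0.025 with no true difference. False non-inferiority is the lower limit of the 95% Wald interval for CC minus SC lying above −10 points when the true CC ADR is 39%.

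| Spurious shift | Superiority error | False non-inferiority |
|---|---|---|
| 1 point towards SC | 0.92% | 0.94% |
| none | 2.31% | 2.40% |
| 0.5 point towards CC | 3.52% | 3.66% |
| 1 point towards CC | 5.20% | 5.42% |
| 2 points towards CC | 10.40% | 10.86% |

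At the 0.2-point shift above, the superiority error is 2.7%. A 1-point shift towards SC lowers the chance of showing non-inferiority, when the ADRs are truly equal, from 95.68% to 91.12%.

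A normal approximation agrees. The standard error is √(2 × 0.49 × 0.51 / 675) = 0.0272, and 1 − Φ(1.96 − 0.01/0.0272) = 5.6% for a 1-point shift, against a nominal 2.5%.

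**The case against.** The strongest reply is that 7.3.5(4) already defines the resection set. A threshold makes sense only if polyps below it are normally left, in both arms, so the gap is one missing sentence. That is a reasonable reading, and the rule is indeed symmetric. But the protocol does not forbid removing smaller distal polyps, and 7.4.1 counts them when they are removed, so the decision stays open.

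Second, no bias is shown. This stands in full. A reader might infer from the table that the trial's type I error is about 5%, or that the design favours CC. The documents support neither: f and g are unknown, g could be zero or of either sign, and plausible small values give a shift of only a few tenths of a point.

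Third, the protocol already plans partial checks. Polyp detection rate (7.4.2) requires detection only, so it does not depend on removal. Section 8.3 breaks adenomas and polyps per colonoscopy down by lesion size and location, and comparing the two by arm could hint at unequal removal. This stands as mitigation. These measures are not an ADR, however, and a joint breakdown by size and site is not stated.

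Fourth, a supportive analysis is commonly left to a SAP, which is not at hand. That would dispose of a complaint about a missing sensitivity analysis alone. Here the defect is in a procedure that the protocol itself fixes incompletely, and the gap is filled after allocation by operators who know the arm.

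The recorded video ("During the colonoscopy, real-time video will be recorded") might seem to offer a direct check. It shows what was on screen, not what the operator noticed, so it cannot reliably separate a missed polyp from one seen and left.

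**Conclusion.** The gap holds on the text: the endpoint counts a class of adenoma whose removal the protocol does not regulate, and an unblinded operator decides. It affects only subjects whose sole adenomas are under 0.6 cm and in the sigmoid, rectosigmoid junction or rectum; the protocol does not give their number.

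Whether it biases the trial, by how much and in which direction cannot be derived from the document. The error rates show sensitivity to assumed shifts, at 675 per arm, an SC ADR of 49% and a margin in absolute points; they are not estimates. What they do show is that about 7 subjects in one arm would roughly double either error rate, which justifies an inexpensive safeguard on the sole primary endpoint. It should be fixed; confidence is medium, because the gap is clear and the harm is only possible.

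**What to change.** 1. **Pre-specify a supportive ADR, by arm,** that counts a subject as positive only for an adenoma in the mandatory-resection set: proximal of any size, or sigmoid, rectosigmoid or rectal of at least 0.6 cm. Size and location are already on the case report form (7.5, item 4), so it also covers subjects enrolled before the change.
2. **Require the non-inferiority and superiority conclusions to be read alongside it.** If the two versions of ADR disagree, the report should say so and should not attribute the difference to detection alone.
3. **Add one sentence to 7.3.5(4)** stating that sigmoid, rectosigmoid and rectal polyps under 0.6 cm are handled the same way in both arms.

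Cost: one sentence and one further analysis of data already collected. Downside: the supportive ADR omits some true small distal adenomas, including any found thanks to the device, and it still relies on the size call of an unblinded operator at the 0.6 cm cut. I would not impose a rule to resect everything at this stage. It could change what ADR counts partway through accrual, would add resections and pathology work, and could not reach subjects already examined.

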#### **7.4.2. Secondary Endpoints**

Secondary endpoints are listed and defined as follows:

- Polyp detection rate (PDR):
  - Percentage of subjects undergoing a complete colonoscopy who have at least one polyp detected.
- Adenomas per colonoscopy (APC):
  - Number of adenomas per colonoscopy, calculated by dividing the total number of adenomas detected by the total number of colonoscopies.
- Polyps per colonoscopy (PPC):
  - Number of polyps of any kind (i.e., adenoma, sessile serrated polyp, hyperplastic polyp, or non-neoplastic polyp) per colonoscopy, calculated by dividing the total number of polyps detected by the total number of colonoscopies.
- Non-neoplastic polypectomy rate (NNPR)
  - Percentage of subjects with at least one non-neoplastic polypectomy at the time of colonoscopy.
  - Non-neoplastic polypectomy (NNP) includes all biopsies or snare polypectomies of lesions on colonoscopy that yield non-adenomatous, non-serrated, and non-hyperplastic tissue upon histologic review.
- Sessile serrated lesions per colonoscopy (SPC):
  - Number of sessile serrated lesions (SSLs) per colonoscopy, calculated by dividing the total number of sessile serrated lesions detected by the total number of colonoscopies.
  - SSLs are not counted into the ADR as recommended by the American Society for Gastrointestinal Endoscopy/American College of Gastroenterology Task Force on Quality in Endoscopy.
- Advanced adenomas per colonoscopy (AAPC):
  - Number of advanced adenomas per colonoscopy, calculated by dividing the total number of advanced adenomas detected by the total number of colonoscopies.
  - Advanced adenomas are defined as adenomas with any of the following features present: high-grade dysplasia, villous features, or endoscopic size  $\geq$  1 cm. Villous features were defined as 25% or more of the composition of the polyp.
- Withdrawal time:
  - The time spent in inspecting the colonic mucosa as the endoscope is withdrawn during a colonoscopy.

## 7.5. Data Collection

The following subject data and relevant information will be collected and recorded using the CRF for each enrolled subject.

### (1) Patient characteristics

- a. Age
- b. Gender
- c. Race
- d. Height
- e. Weight
- f. BMI
- g. Medical history of CRC from any first degree relatives (including parents, siblings, and children)
- h. Smoking

### (2) Disease-related characteristics

- a. Fecal immunochemical test (FIT) results
- b. Colonoscopy indication

### (3) Procedure-related characteristics

- a. Bowel preparation quality (based on the four-grade modified Aronchick Bowel Preparation Scale) ([Hsu et al., 2016](#)): excellent (1), good (2), fair (3), poor (4)
- b. Experience of the operator /endoscopists
- c. Cecal intubation time (min and sec)
- d. Withdrawal time (min and sec)
- e. Effective procedure time (min and sec)
- f. Endoscopy video processor models

### (4) Lesion characteristics

- a. Size
- b. Location
- c. Morphology

### (5) Study outcomes

- a. Number of polyps detected
- b. Number of adenomas detected
- c. Number of sessile serrated lesions
- d. Number of advanced adenomas
- e. Number of non-neoplastic resections

## 8. Statistical Analysis

## 8.1. Sample Size Estimation

The sample size is calculated based on the evaluation of primary outcome ADR. Based on the results of meta-analysis, an expected ADR ranges from around 20% to 40% for AI-aided colonoscopy and SC ([Barua et al., 2021](#); [Hassan et al., 2021](#); [Mohan et al., 2020](#); [Shaukat et al., 2021](#); [Spadaccini et al., 2021](#)). A sample size ranging from 198 to 297 per arm is required to establish non-inferiority with a non-inferiority margin of 10%, power of 80% and an alpha level of 2.5% (one-sided). Considering a withdrawal rate of 10% due to potential exclusions and drop-outs, the enrollment goal is 220 to 330 subjects per arm.

However, interim analysis of this study in March 2023 showed that the ADR in our SC group is 49%, which is significantly higher than the ADR results acquired from meta-analysis (around 20%); therefore, the enrollment goal is increased to 750 subjects per arm. (i.e., 1500 subjects in total. )

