|-----------------------------|-------------------------------------------------------------------------------------------------------------------------------------------------------------------------------------------------------------------------------------------------------------------------------------------------------------------------------------------------------------------------------------------------------------------------------------------------------------------------------------------------------------------------------------------------------------------------------------------------------------------------------------------------------------------------------------------------------------------------------------------------------------------------------------------------------------------------------|
| Statistical Analysis | 
The primary analysis will be the comparison of ADR between an AI-aided colonoscopy and the standard colonoscopy. Differences in ADR between two arms will be expressed as relative risk (RR) with 95% CIs. Non-inferiority will be met for the primary endpoint (ADR) if the lower 2-sided 95% confidence interval (CI) excludes a 10% or greater difference in favor of the control group. The 10% non-inferiority margin reflects a typical maximum clinically acceptable difference for comparative studies. If non-inferiority is demonstrated for the primary endpoint, the endpoint will be assessed for superiority (one-sided p value <0.025) using the Fisher exact test.
                                                                                                                                  |
| Sample Size          | 
The sample size is calculated based on the evaluation of primary outcome ADR. Based on the results of meta-analysis, an expected ADR ranges from around 20% to 40% for computer-aided colonoscopy and SC. A sample size ranging from 198 to 297 per arm is required to establish non-inferiority with a non-inferiority margin of 10%, power of 80% and an alpha level of 2.5% (one-sided). Considering a withdrawal rate of 10% due to potential exclusions and drop-outs, the enrollment goal is 220 to 330 subjects per arm.
 
However, interim analysis of this study performed in October 2022 showed that the ADR in our SC group is 43%, which is significantly higher than the ADR results acquired from meta-analysis (around 20%); therefore, the enrollment goal is increased to 400 subjects per arm.
 |

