## **7. Study Design**

### **7.1. Study Structure**

This study is a prospective, multi-center, parallel-assigned, two-arm, randomized controlled trial. Eligible subjects will be randomly assigned into CC or SC groups in a 1:1 ratio.

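### The printed non-inferiority sample size of 198 to 297 per arm matches a one-sided 5% test, not the stated 2.5%, at which it gives about 70% power instead of 80%

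*Protocol*

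**What the plan says.** Protocol section 8.1 gives a complete set of design inputs and a result.

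- **Expected rate:** "an expected ADR ranges from around 20% to 40% for AI-aided colonoscopy and SC".
- **Result:** "A sample size ranging from 198 to 297 per arm is required to establish non-inferiority with a non-inferiority margin of 10%, power of 80" per cent. The alpha follows in the same sentence: "power of 80% and an alpha level of 2.5% (one-sided"). The Sample Size row of the synopsis (section 3) has the same figures.
- **Withdrawal:** "Considering a withdrawal rate of 10% due to potential exclusions and drop-outs, the enrollment goal is 220 to 330 subjects per arm".
- **Decision rule (section 8.3):** non-inferiority is met "if the lower 2-sided 95% confidence interval (CI) excludes a 10% or greater difference in favor of the control group".
- **Allocation (section 7.1):** subjects are "randomly assigned into CC or SC groups in a 1:1 ratio".

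Both places then raise the goal because the ADR observed in the standard arm exceeded the planning value. The synopsis goes to 400 per arm, citing 43% in October 2022. Section 8.1 goes to 750 per arm, citing 49% in March 2023. Neither shows a calculation for the new goal.

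**The concern.** The lower limit of a two-sided 95% interval is a one-sided 2.5% test, so sections 8.1 and 8.3 and the synopsis agree on the alpha. The sample size does not agree with it: 198 and 297 are too small for 80% power at that alpha.

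This matters because it is the only sample-size calculation in the protocol, and it stands in current text in two places. A reader who wants to judge the later goals of 400 and 750 has nothing else to measure them against. The choice of alpha changes the answer for the 400 goal, which looks ample at 5% and falls slightly short at 2.5%.

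**Working it through.** **Inputs.** Margin 10%, power 80%, one-sided alpha 2.5%, ADR 20% to 40% (section 8.1 and synopsis); 1:1 allocation (section 7.1); 10% withdrawal (section 8.1).

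**Assumptions the protocol does not spell out.** The margin is taken as 10 percentage points, and the true ADR p as equal in both arms.

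**Formula.** Per arm, n = (z_alpha + z_beta)² × 2p(1−p) / 0.10². The factor 2p(1−p)/0.10² is 32 at p = 0.20 and 48 at p = 0.40.

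**Step 1: reproduce the printed figures.** At one-sided 5%, (1.645 + 0.842)² = 6.183.
- p = 0.20: 6.183 × 32 = 197.8, so 198.
- p = 0.40: 6.183 × 48 = 296.8, so 297.

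Both ends match exactly. The inflation is also right: 198/0.9 = 220 and 297/0.9 = 330.

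**Step 2: use the stated alpha.** At one-sided 2.5%, (1.960 + 0.842)² = 7.849.
- p = 0.20: 7.849 × 32 = 251.2, so 252 evaluable; 252/0.9 = 280 enrolled.
- p = 0.40: 7.849 × 48 = 376.7, so 377 evaluable; 377/0.9 = 418.9, so 419 enrolled.

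The printed figures are about 21% too small (198/252 = 0.786; 297/377 = 0.788).

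**Step 3: power of the printed figures at 2.5%.** Power = Φ(0.10/SE − 1.960), with SE = √(2p(1−p)/n).
- n = 198, p = 0.20: SE = √(0.32/198) = 0.0402, and Φ(2.487 − 1.960) = 70.1%.
- n = 297, p = 0.40: SE = √(0.48/297) = 0.0402, again 70.1%.
- If nobody withdrew and all 220 or 330 were analysed, power would be 74.6% at both ends.

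**Step 4: other ways to reach 198 and 297 at one-sided 2.5%.**

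| Variant | ADR 20% | ADR 40% |
|---|---|---|
| Farrington-Manning restricted variance | 255 | 375 |
| Continuity-corrected | 272 | 397 |
| 90% power | 337 | 505 |
| Margin as 10% of the rate (2 or 4 points) | 7.849 × 0.32/0.02² ≈ 6,280 | 7.849 × 0.48/0.04² ≈ 2,355 |

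None gives the printed pair. A superiority formula gives 199 for 20% versus 10% and 294 for 20% versus 30%. That is near but not equal, and it is not the calculation that the protocol describes.

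**Step 5: the later goals at one-sided 2.5%.**

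| Goal per arm | After 10% withdrawal | ADR | Power |
|---|---|---|---|
| 750 (section 8.1) | 675 | 49% | SE 0.0272; Φ(3.675 − 1.960) = 95.7% |
| 400 (synopsis) | 360 | 43% | SE 0.0369; Φ(2.710 − 1.960) = 77.3% |

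At ADR 43%, 80% power needs 385 evaluable (385/0.9, so 428 enrolled) at 2.5%, but only 304 evaluable (304/0.9, so 338 enrolled) at 5%.

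**The case against.** **The figures are superseded.** Section 8.1 itself raises the goal to 750 per arm, where non-inferiority power is about 96%. A reader might infer from the 70% that the trial is underpowered. Section 8.1 does not support that, and no decision rule or type I error rate changes. This objection stands and limits the consequence. It does not make the printed statement true, and it does not cover the synopsis, which still gives 400.

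**The later increases.** A reader might infer that 400 and 750 were scaled up from the faulty base. The text does not say so. It attributes both increases to the observed ADR and shows no calculation linking them to 198 to 297. At ADR 49% and one-sided 2.5%, 393 evaluable per arm would suffice, so 750 is not visibly derived from the earlier figures.

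**Use of 5% is an inference.** The protocol names no formula or software. The exact match at both ends is strong evidence, but the accurate wording is that the figures correspond to 5%, not that 5% was used. The mismatch with 2.5% does not depend on this inference.

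**The assumptions.** Section 8.1 gives one ADR range for both procedures but does not say that the true difference is zero, and section 5 reports a higher ADR with computer-aided detection. A small true benefit would raise power. With 20% against 22% and 198 per arm, SE = √((0.16 + 0.1716)/198) = 0.0409 and power is Φ(0.12/0.0409 − 1.960), about 83%. So the 70% is conditional on equal rates. This does not rescue the printed figures, because a calculation with a benefit built in does not produce 198 and 297. Likewise, section 8.3 expresses the comparison as a relative risk and gives the margin only as 10%. The exact match supports 10 points as the planning reading, but the protocol does not say so.

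**Conclusion.** The point holds as an error in a stated justification. With a margin of 10 percentage points and equal true ADR in both arms, the stated inputs require 252 to 377 evaluable per arm (280 to 419 enrolled). The printed 198 to 297 (220 to 330 enrolled) corresponds to one-sided 5% and gives about 70% power under the rule in section 8.3.

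The effect on the trial depends on which goal governs. If it is 750 per arm, non-inferiority power is about 96% at ADR 49% and is not compromised. If it is the 400 per arm in the synopsis, power is about 77% at ADR 43%, slightly below the stated 80%. All these figures use the normal approximation and the two assumptions above; a relative margin would invalidate them.

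**What to change.** In section 8.1 and the synopsis:

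1. Keep 198 to 297 and 220 to 330 as the initial planning figures, so that the planning history is not rewritten. State that they correspond to one-sided 5% and give about 70% power at one-sided 2.5%.
2. Give the figures for one-sided 2.5% and 80% power: 252 to 377 evaluable and 280 to 419 enrolled per arm. State the assumptions of a 10-point margin and equal true ADR.
3. Reconcile the two enrolment goals (400 in the synopsis, 750 in section 8.1) and state the non-inferiority power of the governing goal at one-sided 2.5%: about 96% for 750 enrolled (675 evaluable, ADR 49%) or about 77% for 400 enrolled (360 evaluable, ADR 43%).

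If 750 governs, the cost is protocol wording only, with no added subjects and no change to the analysis. If 400 governs, the text must either acknowledge the 77% or revisit the goal.

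### The enrolment goal of 750 per arm does not follow from the inputs in section 8.1, and no power or effect is attached to it

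*Protocol*

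**What the plan says.** Protocol section 8.1 starts from the literature: "an expected ADR ranges from around 20% to 40% for AI-aided colonoscopy and SC". It continues: "A sample size ranging from 198 to 297 per arm is required to establish non-inferiority", with a margin of 10%, power of 80% and a one-sided alpha of 2.5%. Withdrawal is then added: "Considering a withdrawal rate of 10% due to potential exclusions and drop-outs, the enrollment goal is 220 to 330 subjects per arm".

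The next paragraph reports an interim SC ADR of 49% in March 2023, "which is significantly higher than the ADR results acquired from meta-analysis (around 20%); therefore, the enrollment goal is increased to 750 subjects per arm", that is, 1,500 in total. It gives no new margin, power, alpha, hypothesis or assumed ADR for computer-aided colonoscopy (CC).

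The synopsis (section 3, Sample Size) has the same opening but a different ending. There the interim look is October 2022, the SC ADR is 43%, and "therefore, the enrollment goal is increased to 400 subjects per arm".

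Section 8.3 tests non-inferiority against a 10% difference without naming the scale, expresses the arm difference as a relative risk, and follows with a one-sided superiority test at 0.025 by Fisher's exact test. No effect size or power is given for superiority.

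**The concern.** The text presents 750 as a consequence of the higher SC ADR. For a fixed absolute margin and equal true rates, the ADR enters the sample size only through p(1 − p). That term is nearly flat between 40% and 60% and is largest at 50%. Going from 43% to 49% raises it from 0.2451 to 0.2499, about 2%, while the goal goes from 400 in the synopsis to 750 in section 8.1, an increase of 87.5%. The ADR alone does not account for that.

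The enrolment target was raised after interim looks, so a reader will want to know what the new number is designed to show. As written, the only power statement belongs to a goal no longer in force, and the two parts of the protocol give different goals.

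**Working it through.** **Inputs.** Margin 10%, power 80%, one-sided alpha 2.5%, withdrawal 10%, planning ADR 20% to 40%, interim SC ADR 49% (section 8.1); interim SC ADR 43% (synopsis); 1:1 allocation (section 7.1). Two assumptions are mine because the protocol does not state them: the margin is in absolute percentage points, and the true ADR is the same in both arms.

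**Formula.** Evaluable n per arm = (z₁₋α + z₀.₈₀)² × 2p(1 − p) / 0.10², rounded up. Enrolled = n / 0.90, rounded up.

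- One-sided 2.5%: (1.9600 + 0.8416)² = 7.849
- One-sided 5%: (1.6449 + 0.8416)² = 6.183

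**Step 1: the protocol's own range.**

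| ADR | One-sided 2.5% (stated): evaluable / enrolled | One-sided 5%: evaluable / enrolled | Protocol: evaluable / enrolled |
|---|---|---|---|
| 20% | 252 / 280 | 198 / 220 | 198 / 220 |
| 40% | 377 / 419 | 297 / 330 | 297 / 330 |

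The printed range matches one-sided 5% exactly and does not match the stated 2.5%. At one-sided 2.5%, 198 (ADR 20%) and 297 (ADR 40%) give about 70% power, not 80%. The exact match at both ends also supports reading the margin as absolute.

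**Step 2: the interim ADRs with the stated inputs.**

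- 43%: 7.849 × 0.4902 / 0.01 = 384.8, so 385 evaluable and 428 enrolled. The synopsis says 400.
- 49%: 7.849 × 0.4998 / 0.01 = 392.3, so 393 evaluable and 437 enrolled. Section 8.1 says 750.
- 50%, where p(1 − p) is largest: 7.849 × 0.5000 / 0.01 = 392.4, so again 393 and 437.

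The goal of 750 exceeds this ceiling by 750/437 − 1 = 72%.

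**Step 3: other readings of the inputs.**

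- One-sided 5%, which generated the original range, at 49%: 310 evaluable, 345 enrolled.
- 90% power at 49%: 526 evaluable, 585 enrolled. 95% power: 650 and 723.
- Relative margin (RR 0.90) at 49%, on the difference scale (0.049): 7.849 × 0.4998 / 0.049² = 1,633.8, so 1,634 evaluable and 1,816 enrolled.
- The same relative margin on the log scale: 7.849 × 2 × (0.51/0.49) / (ln 0.90)² = 1,471.8, so 1,472 evaluable and 1,636 enrolled.

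None of these gives 750.

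**Step 4: what 750 delivers.** 750 × 0.90 = 675 evaluable. At 49% in both arms the standard error is √(0.4998/675) = 0.0272, and 0.10/0.0272 − 1.960 = 1.715, so non-inferiority power is about 96% (95.7%). For comparison, 400 enrolled (360 evaluable) at 43% gives about 77%.

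**The case against.** The ceiling of 437 depends on equal true ADRs. If the SC ADR is 49% and the true CC ADR is 2 points lower, the same margin, alpha and power need 612 evaluable (680 enrolled). At 3 points lower they need 799 (888 enrolled). That range includes 750, so it would be too strong to say that no design with an SC ADR of 49% could lead to 750. This part of the objection stands. However, section 8.1 assumes no CC deficit and gives one ADR range for both techniques, so the goal still does not follow from what is written.

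A second objection is that enrolling more than the minimum does not weaken a non-inferiority conclusion. That is right. It limits the point to how the number is justified, and no bias or type I error consequence is shown.

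Two stronger readings are tempting. A reader might infer that the target was raised to power superiority after seeing the treatment effect, because 675 evaluable per arm would detect 49% versus about 56.6% with roughly 80% power by the normal approximation (about 79% with Fisher's exact test). The protocol does not support this: both accounts of an interim look report an SC ADR only, and no CC ADR, difference or superiority target is mentioned. A reader might also say that comparing 49% with about 20% misstates a planning range that ran to 40%. That range is given for both techniques together, so the text can be read as placing SC near its lower end. The wording is loose, but an error is not shown.

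**Conclusion.** The point holds in limited form. With the stated margin, power, alpha and withdrawal, and assuming an absolute margin and equal true ADRs, an SC ADR of 49% calls for 437 enrolled per arm, not 750. A relative margin does not give 750 either. Reaching it takes an assumption that the protocol does not state, such as power near 96%, a smaller margin, a CC deficit of 2 to 3 points or a superiority target, and the document gives no ground for choosing among these.

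Two linked errors belong with it. The original range does not match its stated alpha, and the synopsis and section 8.1 give different goals (400 and 750), the lower of which is also short of the 428 that the stated inputs give at 43%.

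This should be fixed, but it does not threaten the primary non-inferiority test, which 750 per arm more than covers under these assumptions.

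**What to change.** Wording only, with no change in enrolment:

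- In section 8.1, replace the sentence that derives 750 from the SC ADR with the actual basis: assumed SC and CC ADR, hypothesis, margin and its scale, alpha and power.
- State that 750 enrolled, about 675 evaluable, gives about 96% non-inferiority power for a 10-point margin at one-sided 2.5% with 49% in both arms.
- If superiority was the target, give the CC ADR that was in fact assumed at the time and the power under Fisher's exact test. An effect worked backwards from 750, such as 56.6%, should not be entered as if it had been planned.
- Correct the original range to 252 to 377 evaluable (280 to 419 enrolled), or correct the alpha stated for it.
- Align the synopsis with section 8.1 on the interim date, the SC ADR and the goal. If both interim looks are kept as history, give them in order and mark which goal is in force.

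The cost is a protocol text amendment. The sponsor has to recover the reasoning used in March 2023, or say plainly that 750 was not derived from a power calculation.
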